## Abstract

**Background:**

Chronic venous insufficiency, in its final stage can cause venous ulcers. Venous ulcers have a prevalence of 0.5 % to 0.8 % in the general population, and increases starting at 60 years of age. This condition often causes increased dependency in affected individuals, as well as a perceived reduced quality of life and family overload.

Local Treating chronic venous ulcers has 2 components: topically healing the ulcer and controlling the venous insufficiency. There is evidence that compressive therapy favours the healing process of venous ulcers. The studies we have found suggest that the use of multilayer bandage systems is more effective than the use of bandages with a single component, these are mostly using in Spain. Multilayer compression bandages with 2 layers are equally effective in the healing process of chronic venous ulcers as 4-layer bandages and are better tolerated and preferenced by patients. More studies are needed to specifically compare the 2-layer bandages systems in the settings where these patients are usually treated.

**Method/design:**

Randomised, controlled, parallel, multicentre clinical trial, with 12 weeks of follow-up and blind evaluation of the response variable.

The objective is to assess the efficacy of multilayer compression bandages (2 layers) compared with crepe bandages, based on the incidence of healed venous ulcers in individuals treated in primary care nursing consultations, at 12 weeks of follow-up.

The study will include 216 individuals (108 per branch) with venous ulcers treated in primary care nursing consultations.

The primary endpoint is complete healing at 12 weeks of follow-up. The secondary endpoints are the degree of healing (Resvech.2), quality of life (CCVUQ-e), adverse reactions related to the healing process. Prognosis and demographic variables are also recorder.

Effectiveness analysis using Kaplan-Meier curves, a log-rank test and a Cox regression analysis. The analysis was performed by intention to treat.

**Discussion:**

The study results can contribute to improving the care and quality of life of patients with venous ulcers, decreasing healing times and healthcare expenditure and contributing to the consistent treatment of these lesions.

**Trial registration:**

This study has been recorded in the Clinical Trials.gov site with the code NCT02364921. 17 February 2015.

## Background

### Aging and chronicity

Spain, as with other developed countries, is experiencing a progressive ageing of the population (according to the National Institute of Statistics). In 2052, the over-64 age group increased by 7.2 million, accounting for 37 % of the total population [1], contributing to an increase in chronic diseases, including chronic venous insufficiency.

In chronic venous insufficiency, the venous system of the legs is ineffective in performing venous return, and there is venous reflux due to valve failure, physical inactivity and cardiovascular problems, which lead to an increase in pressure within the veins and venous hypertension.

Chronic venous insufficiency covers a series of signs and symptoms including varicose veins, varicules, oedema, skin lesions and ulcers.

The DETECT-IVC study conducted in Spain found that 71 % of individuals in primary care consultations had some sign or symptom related to chronic venous insufficiency [2].

### Venous ulcers. Prevalence and repercussion of the problem

Venous ulcers are lesions skin loss that rest on the skin affected by stasis dermatitis, secondary to severe chronic venous insufficiency [3]. They are mainly located in the internal lateral area of the distal third of the leg. To diagnose this condition, is necessary a physical examination to confirm the presence of tibial pulses and/or a pressure gradient in the feet >60 mmHg and/or an ankle brachial index >0.8 to rule out an arterial origin [4].

Ambulatory venous hypertension represents the start of the pathophysiology of venous ulcers. The most common trigger for ulceration is trauma on the preulcerative lesions; however, the ulcers often start spontaneously on the lesions [5].

Ulcers of venous aetiology constitute between 75 and 80 % of all ulcers. They have a prevalence of 0.5 % to 0.8 % in the general population and an incidence of between 2 and 5 new cases per thousand individuals per year [4]. The female to male ratio is 3:1, and increases starting at 60 years of age [5].

The DETECT-IVC study in Spain [2] showed that 2.5 % of individuals in primary care consultations have venous ulcers. This rate increases for women and the elderly; 2 % of patients were hospitalised and 2.5 % took time off from work.

The median healing time for chronic venous ulcers varies between 75 and 90 days [6]. Half of all healed ulcers recur at 12 months of healing. Pre-existing skin disorders are a risk factor in the incidence of new relapses [5, 6].

These ulcers have abundant exudate, are often foul smelling, can get infected and cause moderate pain, which coupled with slow healing and frequent relapses affect the quality of life of patients with these ulcers [7].

### Treatment of venous ulcers. Compression bandages

Treating chronic venous ulcers requires a comprehensive approach for the patient, by treating the aetiological factors that determine their evolution, such as venous insufficiency, diet, physical inactivity and postural measures.

Local treatment has 2 components: topically healing the ulcer and controlling the venous insufficiency through the use of compressive therapy.

Evidence suggests that the wound should be treated with moist wound healing, with dressings to control the exudate and perilesional skin moisturising [8].

There is evidence that compressive therapy favours the healing process of venous ulcers. Borges et al., in a systematic review of 33 primary studies and 2 meta-analyses that included more than 1000 patients, concluded that compressive therapy increases the healing rate of venous ulcers [8]. O’Meara S et al. performed a systematic review to compare the effectiveness of using some type of compression bandages versus not using any pressure in the healing of venous ulcers and compared the effectiveness of various types of compression. The authors included 48 clinical trials with 4321 patients and concluded that compressive therapy contributes to improving the flow of venous return, decreases oedema and pain and favours the healing process of venous ulcers [9].

There are various types of compression bandages. They are classified according to the type of material (elastic/inelastic), degree of pressure (light, medium, high) and number of layers (single layer/multilayer) [10]. The light compression elastic single-layer bandages and the crepe bandage offer low pressure (15–20 mmHg for the ankle). Multilayer bandages of 2, 3 or 4 layers can combine elastic or inelastic components, reaching a pressure of 40 mmHg at the ankle.

### Advantages and disadvantages of the various types of compression

The single-layer elastic bandages with light compression maintain the necessary pressure level for 1 h, do not control the exudate and can result in overpressure when applying them and are therefore considered fixing bandages [11, 12].

Multilayer bandages are effective both at rest and in motion, they reduce the calibre of superficial and deep veins, promote venous flow, reduce oedema, improve the effect of the muscle pump of the lower legs and reduce orthostatic flow, residual volume and venous pressure by improving the operation of venous valves [13].

Various studies have compared the efficacy of the different compression therapy systems in the healing of chronic venous ulcers. O’Meara et al. performed a systematic review to compare the efficacy of 2 types of compression bandages: multilayer bandages with 4 layers and short-stretch bandage. The authors included 5 clinical trials with 797 patients. They concluded that 4-layer compression bandages are associated with a shorter healing time. The authors recommended performing more studies to compare the compression bandage systems, using a system to blind the assessment of the response variables [6].

Another study compared multilayer compression bandages with 2 and 4 layers in terms of the pressure achieved under the bandages and patient tolerance. The study found no differences in the pressure achieved by the 2 types of compression, but the 2-layer compression bandage was better tolerated by the patients [14].

Moffatt et al. compared the complete healing rate at 8 weeks of follow-up, the quality of life and the patients’ preferences when using 2 types of compression bandages (2 and 4-layer). The authors found no differences in the complete healing rate; however, the overall quality of life score and the preferences were significantly higher for patients who used the 2-layer bandages [15].

It has been estimated that treating venous ulcers generates high direct and indirect costs, increased consultations in primary care and hospitalisations. Topical and systemic treatments, represents approximately 2 % of the healthcare expenditure in Spain and neighbouring countries [2].

Published literature suggest that the use of multilayer bandage systems is more effective than the use of bandages with a single component, although the majority of the studies included 4-layer bandages. Moreover, multilayer compression bandages with 2 layers are equally effective in the healing process of chronic venous ulcers as 4-layer bandages and are better tolerated by patients who express a preference for the 2-layer bandages [15].

More studies are needed to specifically compare the 2-layer bandages systems in the settings where these patients are usually treated, using blinding techniques to assess the response variable.

In our region, light compression single-layer elastic bandages (crepe bandages) are commonly used. We are not aware of any study in Spain that has specifically compared the effectiveness of 2-layer compression bandages versus the single-layer elastic light compression bandages commonly used in health centres.

We propose this study to compare the effectiveness of 2-layer compression bandages versus crepe bandages in the healing of venous ulcers and determine how they affect the quality of life of individuals with this problem.

### Aim

The aim of this study is to assess whether multilayer compression bandages with 2 layers are more effective than crepe bandages in the healing of chronic venous ulcers in patients treated in primary care nursing consultations, measured by the incidence rate of ulcers with complete healing at 12 weeks of follow-up in each group.

The secondary objectives are to compare the effectiveness of the multilayer and crepe bandages (based on the degree of healing achieved and measured with Resvech 2.0), assess improvements in quality of life (measured with the Charing Cross Venous Ulcer Questionnaire [CCVuQ-e]) and analyse the sociodemographic, clinical and treatment factors associated with complete healing of venous ulcers.

## Methods/design

### Study design

Randomised, controlled, parallel, multicentre clinical trial, with 12 weeks of follow-up and blind evaluation of the response variable.

The study involves 22 primary healthcare centres in the Madrid region of Spain.: La Paz, Arganda, Artilleros, Buenos Aires, Federica Montseny, José Maria Llanos, Pavones, Rafael Alberti, Torito,. Villa de Vallecas, Villablanca, Villarejo de Salvanés, Mejorada del Campo, Jaime Vera, Los Alperchines, San Fernando II, [name], Cerro Almodovar, Ibiza, Valdebernardo, Vicente Soldevilla and Morata de Tajuña. The last six centres were added later to the study, in order to achieve the required number of patients to recruit, being approved by the Ethics Committee.

Sixty one volunteer nurses will participate in the study. The nurses will conduct the intervention.

The investigator will properly inform all study participants and will request their written, signed and dated informed consent. The investigator will provide complete and appropriate verbal and written information on the nature, purpose and potential risks and benefits of their participation in the study.

### Participants

Participants older than 18 years with chronic venous ulcers who attend to a primary care nursing consultation.

#### Inclusion criteria

Over 18 years of age.Individuals with a diagnosis of venous ulcers of more than 6 weeks of evolution. If the participant has more than one lesion, the nurse will select the lesion with the highest Resvech score for the study.Presence of an ankle brachial index (ABI) greater than 0.8 and less than 1.3.Individuals who able to follow the demands of the trial and who provide their written informed consent to participate.

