### Blinding

It is not possible to blind the intervention in this type of study. The measurement of the primary endpoint, degree of healing, will be conducted by nurses who are unaware of the type of intervention applied to the patient. The analysis will be performed by practitioners who are unaware of the assignment.

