**Fig. 2 Fig2:**
[figure not shown]
Sequence of visits in Control and Experimental Group

The schedule of visits is shown in Table 1.

**Table 1 Tab1:** Schedule of visits

	Baseline visit Day 0	Visit 1 Day 1	Visit 2 Day 15	Visit 3 Day 30	Visit 4 Day 45	Visit 5 Day 60	Visit 6 Day 75	Visit 7 Day 90 End of follow-up
Verification of inclusion criteria	x							
Patient has signed the informed consent	x							
Randomisation	x							
Intervention		x	x	x	x	x	x	x
Resverch assessment		x	x	x	x	x	x	x
CCVUQ-e questionnaire		x						x
Collecting data on adverse reactions			x	x	x	x	x	x
Healing complete			x	x	x	x	x	x
Sociodemographic variables	x							
Prognostic variables		x						
Variables related to healing		x	x	x	x	x	x	x

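### The schedule puts the first Resvech, CCVUQ-e and prognostic recordings one day after open randomisation, although choosing the index ulcer at the Day 0 eligibility check requires a Resvech score

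*Protocol article*

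**What the plan says.** The *Inclusion criteria* deal with patients who have several ulcers: "If the participant has more than one lesion, the nurse will select the lesion with the highest Resvech score for the study".

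Table 1 (schedule of visits) has a column headed "Baseline visit Day 0". It holds "Verification of inclusion criteria", consent, randomisation and "Sociodemographic variables". The rows "Resverch assessment", "CCVUQ-e questionnaire" and "Prognostic variables" have no mark there. Each has its first mark at Visit 1, Day 1, the column in which the intervention also starts.

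On masking, the *Blinding* section says: "It is not possible to blind the intervention in this type of study". It adds that degree of healing is measured by nurses who do not know the bandage used. The *Discussion* says that patients are recruited and treated by their own reference nurses. *Random assignment* says that the allocation is generated automatically when patient data are entered in the eCRF; it does not say which data must be entered first.

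**The concern.** Randomisation protects a baseline value, or the choice of the unit to be followed, only if it is fixed before anyone involved can know the arm. On the schedule as printed, two things lack that protection.

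- **Index ulcer.** The selection rule needs a Resvech score for each lesion, and the first scheduled score comes after allocation. If the choice waits for that score, a nurse who knows the arm could affect which ulcer is followed. The main outcome, complete healing at 12 weeks, is scored on that ulcer. A blinded assessor protects the scoring of an ulcer already chosen, not the choice itself.
- **Starting CCVUQ-e.** This is the patient's own report in an open trial, and its only value before the end of follow-up is on Day 1. The *Aim* includes improvement in quality of life, which needs a starting value untouched by knowledge of the bandage.

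The prognostic variables are also first recorded on Day 1. They are candidates for the Cox adjustment described under *Analysis*, and the comparison of the groups at the start of the trial would rest on Day 1 values for these items.

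**Working it through.** **Schedule set against the rules that depend on it**

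| Item | First mark in Table 1 | Needed by | Before allocation? |
|---|---|---|---|
| Eligibility check (includes age, ABI, duration over 6 weeks) | Day 0 | Enrolment | Same visit as randomisation; order within the visit not stated, but enrolment implies yes |
| Sociodemographic variables | Day 0 | Group description | Same visit; order not stated |
| Randomisation | Day 0 | – | – |
| Resvech | Day 1 | Index-ulcer choice (an inclusion criterion); degree of healing | No |
| CCVUQ-e | Day 1, then Day 90 | Improvement in quality of life | No |
| Prognostic variables | Day 1 only | Possible Cox adjustment | No |

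1. The selection rule is among the inclusion criteria, and Table 1 verifies these only at Day 0. Read that way, the ulcer is chosen at Day 0.
2. The rule is defined by Resvech, and Table 1 schedules no Resvech at Day 0. Read that way, the score that decides the choice is first scheduled at Day 1.
3. Both cannot be followed as written. Either an unscheduled score is taken at Day 0, with no scheduled record of it, or the choice is made after allocation.
4. *Random assignment* does not settle this. It conceals the sequence from the person enrolling, but does not make entry of the index ulcer a condition for releasing the arm.

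**The plan's own figure, as a yardstick**

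Inputs from *Sample size*: 58% healed with multilayer bandages, a difference of 20 points (read as 58% against 38%), alpha 0.05 (taken as two-sided), power 80%, loss 10%. With pooled variance and mean proportion 0.48:

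n = [1.960 × √(2 × 0.48 × 0.52) + 0.842 × √(0.58 × 0.42 + 0.38 × 0.62)]² / 0.20² = 96.8, so 97 per group; 97 / 0.9 = 107.8, so 108.

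Both stated figures reproduce. This point does not touch the sample size; 20 points is simply the scale for what follows.

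**Illustration for the index ulcer (all inputs assumed)**

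The document gives neither the share of patients with several ulcers nor the difference in healing between their lesions. The shift in one arm's healed proportion is:

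shift = P(several ulcers) × P(a different lesion is picked, in one arm only) × difference in healing between the lesions

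- Low end: 0.25 × 0.10 × 20 points = 0.5 points.
- High end: 0.40 × 0.50 × 20 points = 4.0 points, one fifth of the planned difference.

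The direction is not known. The high end needs half of the multi-ulcer patients in one arm to get a different lesion despite a fixed highest-score rule, which is a demanding assumption.

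**CCVUQ-e**

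If knowing the arm shifts the mean starting score in one arm by d, a baseline-adjusted difference moves by b × d, where b is the slope on baseline; for a simple change score b = 1. The document gives neither b nor d, nor does it specify either analysis.

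**The case against.** Much can be said on the other side, and a good part of it stands.

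- **Lesion choice is probably meant to come first.** The rule is an inclusion criterion, *Data collection* has patients checked against all the criteria when they accept, and the eCRF allocates after some data are entered. A reader might infer from Table 1 that the document places the choice of ulcer after allocation. It does not say so: a missing mark does not prove that no score is taken. What remains is that the schedule and the rule disagree and no scheduled record fixes the choice beforehand.
- **The Day 1 Resvech may be a blinded value.** Resvech is the degree-of-healing measure, and *Blinding* assigns that measurement to nurses unaware of the bandage. The section does not say who scores Day 1, so bias in that score cannot be presumed. Nor does it say that those nurses choose the ulcer.
- **Discretion is narrow.** The rule is fixed and matters only with more than one lesion. Location, number of ulcers, recurrence and place of care are largely factual.
- **The primary comparison does not use these baselines.** The incidence-rate ratio and the log-rank test need neither baseline Resvech nor baseline CCVUQ-e, and neither is named as a Cox covariate. The only route to the primary result is the choice of ulcer and, less directly, the prognostic variables in the Cox model.

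A condensed article may omit detail, but Table 1 positively places these marks at Day 1. That is a stated schedule, not an omission.

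**Conclusion.** The point holds in a limited form. Followed as written, Table 1 yields a patient-reported CCVUQ-e baseline taken after open allocation and prognostic variables recorded after it. It also contains no scheduled Resvech that could fix the index ulcer before the treating nurse can know the arm. The inclusion criteria and Table 1 must be reconciled.

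A reader might go further and infer that every baseline value is exposed to allocation bias. The document does not support that: sociodemographic variables and the eligibility items (age, ABI, duration over 6 weeks) are at Day 0.

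The size of any bias cannot be estimated from the document. The 0.5 to 4 points above rest wholly on assumed inputs and apply only if the ulcer is in fact chosen after allocation. The CCVUQ-e problem does not depend on that condition, but it concerns a secondary outcome. This should be fixed because the remedy is nearly free and later analysis could not undo an arm-dependent choice of ulcer; it is not a reason to doubt the design as a whole.

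**What to change.** In Table 1, move the first Resvech (scored for all lesions), the index-ulcer selection, the CCVUQ-e and the prognostic variables to the Day 0 visit, and state that they come before randomisation. Set the eCRF to release the allocation only after these items are entered. State in the *Inclusion criteria* or *Blinding* section who scores the first Resvech and who selects the ulcer.

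For patients already enrolled, eCRF time stamps, if kept, could show whether the ulcer was recorded before the arm was released.

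The cost is one table edit and an order check in the eCRF. The measurements are already planned, so no visit, staff or patients are added, and the sample size of 108 per arm is unchanged.

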#### Exclusion criteria

Related to contraindications for compression therapy: Patients diagnosed with poorly controlled diabetes mellitus (latest HbA1c according to the recommendations of American Diabetes Association (ADA) and European Association for the Study of Diabetes (EASD) [16]), on treatment with antineoplastic agents, with decompensated heart failure, acute phase dermatitis, at the time of the study, rheumatoid arthritis, acute phase deep vein thrombosis, with mixed ulcers or patients who are simultaneously participating in another clinical trial.

### Sample size

Earlier studies have achieved complete healing rates at 12 weeks of follow-up of 58 % by employing multilayer bandages. For an alpha error of 0.05 and a beta error of 0.2 (80 % power) and to detect a minimum difference of 20 % between the 2 groups, a total of 97 patients will be needed in each group. Estimating a 10 % loss rate at 3 months, at least 108 patients will be included in each study branch.

The patients will be consecutively included in the study. The recruitment will be competitive until the sample size is reached.

### Random assignment

Randomisation sequence: The randomisation will be performed automatically by inserting the patients’ data into the electronic case report forms (eCRF).

Lack of knowledge of the randomisation sequence by the professional who enrols the patients will therefore be ensured.

Patient recruitment is shown in Fig. 1.

**Fig. 1 Fig1:**
[figure not shown]
Patient Recruitment. Patients diagnosed with venous ulcers and who meet the inclusion criteria

